# Evaluating the effectiveness and implementation of evidence-based early-life nutrition interventions in a community setting a hybrid type 1 non-randomized trial – the Nutrition Now project protocol

**DOI:** 10.3389/fendo.2022.1071489

**Published:** 2023-01-10

**Keywords:** digital diet intervention, early life obesity prevention, maternal and child health care, implementation, feeding practices, municipality scale up, the Nutrition Now project protocol

## Abstract

**Clinical Trial Registration:**

https://www.isrctn.com/, identified ISRCTN10694967.

## 1 Introduction

Research on the effectiveness of dietary interventions and their public health impact in real-world, high-income settings is scarce (1). Further, only a fraction of efficacious health interventions have been successfully scaled up and implemented in real life settings (2). This represents a clear evidence-to-practice gap, with a loss of opportunity to improve practice and an unnecessary waste of resources (3).

The first 1000 days of life, from conception until a child’s second birthday, is a window of opportunity for promoting long-term health and well-being (4). Failure to meet nutritional needs in this period is strongly linked to raised lifelong risk of obesity and non-communicable diseases (NCDs) (5). The importance of diet-related interventions in the first 1000 days can be ascribed to at least three mechanisms operating at different levels. First, unmet demands in this critical phase of early development can affect the size and structure of organs, increasing the risk of developing hypertension, cardiovascular disease, type 2 diabetes, and obesity (6). Extensive growth and neurodevelopment take place in this period, and optimal development depends on the amount and quality of food and nutrients provided (4, 7). Second, adverse nutritional conditions may permanently affect gene expression and program the body towards the development of NCDs (8). Third, dietary preferences and food habits are formed early in life, influenced by feeding practices of parents and others, the variety of foods offered (9), and the socioeconomic, cultural and educational context of the family (10). The public health significance of the first 1000 days is supported by cost-benefit and cost-effectiveness analyses showing large economic and social returns from early-life investment, especially from optimising nutrition (11).

The World Health Organization (WHO) promotes a lifecourse approach to promoting health and eradicating health inequality (12). A lifecourse approach to nutrition focuses on targeting nutrition during sensitive dietary transitions, such as the initiation and maintenance of breastfeeding, the introduction of complementary foods, and the transition to early childhood education and care (ECEC) when meals are eaten outside the home environment and shared with peers (13). These transitions need to be acknowledged and addressed through primary care and an education system, which aims to give parents and ECEC providers knowledge and skills to support their children to acquire dietary habits that promote rather than constrain their future health.

The Norwegian government sets goals to improve population diet and dietary habits in the Norwegian National Action Plan for a Healthier Diet (2017–21), which has since been extended to 2023 (14). The mid-term evaluation report, launched in June 2020, reveals that Norway is not on track to reach these goals and that much remains to be done in all age groups (15). One example is the large increase in the use of commercial baby food pouches, which rose from no usage in 2008 to 61% of 6 months old receiving them almost every day in 2020 (16, 17). These pouches are convenient, but their contents are often high in sugar (18, 19). Frequent use of such products limits texture and flavour learning, prevents use of healthy feeding practices such as responsive feeding, and increases the risk of childhood obesity (18). The inadequate and sometimes complete lack of vegetables served in ECEC settings is another example (20). Further, unacceptably large differences exist across socioeconomic groups regarding diet during pregnancy, infant and child feeding practices and overall diet quality (21, 22).

Dietary care is a complex part of child rearing. Hence, many parents seek out information on diet and feeding practices, some from questionable sources such as social media influencers (23, 24). There is a potential role for primary health services (Maternal and Child Health (MCH) care) to support parents to develop appropriate skills in feeding their child, regardless of background. The INFANT study demonstrated an untapped potential for integrating flexible, evidence-based e-learning resources to support in-person food-based dietary guidance (25). ECEC is another municipal service that is important for child diet, and which represents an opportunity to enhance meal interactions and diet quality. In Norway, most children from 1 to 5 years attend ECEC, including almost 90% of 1–2-year-olds (26). Throughout a child’s total time spent in ECEC an estimated 3000-4000 meals are eaten. Thus, ECEC offer an important setting for exposure to healthy foods; staff’s feeding style and practices may play a significant role in establishing early healthy eating habits in Norway’s children (27). Stakeholders at municipality level can support citizens’ adoption of a healthy diet early in life through strategies, prioritizing efforts and resources that enhance health and wellbeing in target groups.

We have previously developed and reported on the efficacy of four interventions that target diet during pregnancy, parental feeding practices, and ECEC diet quality and meal environment, respectively. All four interventions have shown promising indications of dietary improvement (28–32) (**Additional File 1, Table S1**). These interventions are digital, largely video-based and grounded in social cognitive theory (33), addressing the interaction between person, environment, and behaviour. In the Nutrition Now project, we have combined these four interventions into one joint e-learning resource (the Nutrition Now resource) for parents, MCH staff and ECEC staff. The Nutrition Now resource will be implemented in one municipality through municipal services for MCH care (age: 0-2 years) and ECEC departments for children aged 1-3 years, as shown in **Figure 1**, which depicts hypothesised mechanisms to explain how the intervention may work. Increased knowledge, skills, and motivation are thought to improve dietary behaviors and feeding practices that will in turn affect pregnancy, infant and toddler health outcomes. We also aim for the implementation to influence local policy relating to physical and social aspects of the food environment. The ultimate goal of the Nutrition Now project is to reduce the burden of obesity and NCDs and improve health in quality of life in Norway through improved diet and diet-related behavior in the first 1000 days of life (**Figure 1**).

**Figure 1 f1:**
[figure not shown]
Logic model for Nutrition Now.

The Nutrition Now Project comprises two studies, with the results of the first informing the second. The field of dissemination and implementation research is constantly evolving. While the established standards of evidence for efficacy, effectiveness and scale-up research (34) have more distinct phases of effectiveness and implementation, newer hybrid designs propose to increase the speed of moving research into practice by blending the two stages of effectiveness evaluation and implementation, emphasising either effectiveness or implementation dependent on the type of hybrid study. The current study is a hybrid type 1 study [according to criteria from Curran et al. (35) and Landes et al. (36)] focused primarily on evaluating the effectiveness of providing access to the Nutrition Now resource, and secondly on evaluating implementation and cost-effectiveness. The subsequent study will be a hybrid type 3 study with a primary focus on implementation outcomes (35, 36). Scale up of the Nutrition Now resource to county level will be described in a later paper.

## 2 Methods/design

### 2.1 Aims and objectives

The aim of the study is to assess the impacts on child diet quality of implementing an e-learning resource (the Nutrition Now resource) comprising four digital interventions of known individual efficacy in a community setting.

The three main objectives are to a) evaluate the effectiveness of the Nutrition Now resource on outcomes related to diet and diet-related behaviors in early life, with special attention to the influence of socio-economic position b) observe and gather information on the implementation process to identify implementation strategies for use in a forthcoming scale up, with a special focus on ethnic minority groups and c) perform both trial- and model-based economic evaluations of the implemented Nutrition Now resource.

### 2.2 Outcomes

The outcomes from this study are divided into three main categories: effectiveness outcomes, implementation outcomes, and outcomes from the economic evaluation (**Figure 2**). The effectiveness and implementation outcomes are measured on both the individual, organisational, and community level. An overview of all outcomes, the evaluation data relating to these outcomes, the level of measurement, and the instruments that will be used to collect the data is shown in **Table 1**.

**Figure 2 f2:**
[figure not shown]
Overview of assessments, participants, and types of outcome measures in the mixed methods Hybrid 1 trial of the Nutrition Now project. **(A)** Ethnic minorities invited to participate in qualitative interviews in addition to the assessment that applies to all recruited pregnant women/parents of 0-2 year-olds. **(B)** ECEC staff champions and MCH staff contact persons are appointed staff members invited to participate in short iterative interviews. **(C)** ECEC leaders provide socio-demographic data for the effectiveness evaluation to be assessed at the ECEC level in addition to qualitative interviews.

**Table 1 T1:** Effectiveness, implementation and cost-effectiveness outcomes in Nutrition Now.

Outcomes	Evaluation data	Data collection tool	Level
Effectiveness			
Aspects of child diet quality^1^	Frequency of intake of fruits, vegetables, pulses, and sugary drinks.	Short food frequency web-based questionnaire.	Individual
Breastfeeding^2^	Intention of breastfeeding, exclusive breastfeeding duration and any breastfeeding duration	Short web-based questionnaire	Individual
Child eating enjoyment^2^	Child Eating-enjoyment, reported by parents and ECEC staff	Child eating-enjoyment scale (37)	Individual
Child quality of life^2^	Pediatric Quality of Life Infant Scales	PedsQL (38) – Web-based questionnaire	Individual
Child development^2^	Developmental milestones	Ages and stages (18 months) ASQ3 (39)	Individual
Anthropometric measures (mother, child) ^2^	Weight change in pregnancy, mother’s weight and height, child’s weight and length	Short digital web-based questionnaire	Individual
Pregnancy complications	Preeclampsia, gestational diabetes, preterm delivery		Individual
Maternal diet in pregnancy^2^	Diet quality score	Diet screener, web-based questionnaire	Individual
Maternal quality of life^2^	Satisfaction with life score	SWLS - Satisfaction with life scale (40) – Web-based questionnaire	Individual
Parental meal- and feeding practices^2^	Role modelling, responsive feeding, family meal participation, meal distractions, frequency of home cooking, repeated exposure.	Short digital web-based questionnaire	Individual
ECEC staff meal- and feeding practices^2^	Role modelling, meal practices, repeated exposure, collaboration with parents.	Short digital web-based questionnaire	Individual/organizational
ECEC fruit and vegetable availability^2^	Fruit and vegetables purchases in ECEC	Receipts collected retrospectively, digital when available.	Organizational level
Municipal spend on nutrition ^2^	Resources (staff/money) allocated to nutrition or food-related activities over the annual budget in the municipality.	Publicly available political protocol documents. Collected retrospectively.	Community level
Implementation			
Acceptability	Whether Nutrition Now is liked, welcomed, appealing and approved	AIM-scale (41) Web-based questionnaire Interviews	Individual (a,b,d), and organizational (e,f,g)
Appropriateness	Whether Nutrition Now is fitting, suitable, applicable and a good match	IAM-scale (41) Web-based questionnaire Interviews	Individual (a,b,d), and organizational (e,f,g)
Feasibility	Whether Nutrition Now is implementable, possible, doable and easy to use	FIM-scale (41) Web-based questionnaire Interviews	Individual (a,b,d) and organizational (e,f,g)
Reach	Number of users (incl. ECEC) and characteristics of users	Data from website	Individual and organizational
Adoption/Uptake	Number of participants (incl ECEC)/number invited, what parts of the resources are used, and for how long.	Data from recruitment Interviews	Individual (a,b) and organizational (e,f,g)
Implementation/Fidelity	To what extent Nutrition Now is delivered as planned	RE-AIM.org (42) Interviews	Individual (a,b) and organizational (e,f,g)
Maintenance/Sustainability	To what extent Nutrition Now is still being used 7 and 12 months after implementation, how it is adapted.	RE-AIM.org (43) Interviews	Individual (a,b), organizational (e,f,g), community.
Cost-effectiveness			
Implementation costs	Costs of implementing the e-resource, including monitoring activities and management. Costs of the time spent by MCH and ECEC staff in using the resource.	Implementation costs/effectiveness outcomes	Organizational
Nutrition Now effectiveness outcomes	Quality of life score and developmental milestones.	PedsQL, Ages and stages (18 months) ASQ3 (39) in short digital questionnaire	Individual

^1^ Primary effectiveness outcome, ^2^ Secondary effectiveness outcome. Implementation outcomes will also be assessed in qualitative interviews. Level: Individual: ECEC staff (a), Health care center staff (nurses and midwifes) (b), pregnant women (c), parents of 0-24 months old children (d).

Organizational: ECEC leader (e), health care center leader (f), municipality (g), Community: network of public, voluntary and commercial stakeholders, including inhabitants in the municipality.

#### 2.2.1 Effectiveness outcomes

The primary effectiveness outcome is aspects of child diet quality, represented by intake of vegetables, fruits and berries, legumes/pulses and sugar sweetened beverages. Secondary outcomes include a) breastfeeding rates (including mixed feeding), b) child eating enjoyment c) health-related quality of life (infant), d) child development measures, e) self-reported anthropometrics (parental and child), f) maternal diet, g) maternal quality-of-life measures h) pregnancy complications, i) parental feeding practices, j) ECEC staff feeding practices k) ECEC fruit and vegetable availability and l) municipal spend on activities related to early childhood nutrition and feeding practices (see **Table 1**).

#### 2.2.2 Implementation outcomes

Seven outcomes will be used to evaluate the implementation process, including i) reach, ii) adoption, iii) implementation (fidelity), and iv) maintenance, as defined by RE-AIM (44, 45), and v) acceptability, vi) appropriateness and vii) feasibility, as defined by Proctor et al. (46) (**Table 1**). In addition, we will specifically assess adoption, acceptability, appropriateness, and feasibility in an ethnically diverse sample.

#### 2.2.3 Cost-effectiveness outcomes

The cost-effectiveness outcomes that will be evaluated are implementation costs in relation to the effectiveness outcomes child health-related quality of life and development measures.

### 2.3 Study design

In this hybrid type 1 mixed methods implementation study we use a quasi-experimental design. The CONSORT Extension for pragmatic trials with its checklist was used (47). A single intervention municipality will be given access to the Nutrition Now resource and another control municipality (non-equivalent control) will continue as normal (**Figure 2**). Data from participants resident in the intervention municipality will be collected in the form of a pretest before they are given access to the Nutrition Now resource. Subsequently post-test data will be collected until the child reaches 2 years of age (See Data collection). Participants in the control municipality will be asked to provide pre- and post-test data but will not receive access to the Nutrition Now resource. Additionally, a time-series design will be used for comparisons within the intervention municipality between groups of participants exposed to the Nutrition Now resource at different levels of duration, and different types of exposure (See Data collection).

Enrolment started September 2022. The anticipated recruitment period is from September 2022-to April 2023, and we envision that the last participant (if recruited in early pregnancy in April 2023) will complete the study in September 2025. The ECECs were recruited prior to September 2022 and MCH personnel and parents will be recruited autumn 2022.

Intervention municipality provision of access to the Nutrition Now resource starts upon enrollment in the study and is expected to continue beyond the study period as long as the municipality finds it useful.

### 2.4 Setting

The intervention and control municipalities are situated in different counties in coastal areas in the south of Norway. They have broadly comparable demographics: for example, they are comparable with respect to population size (appr. ~46000 inhabitants), number of births per year (~400), number of ECECs (54 vs 39) as well as education level, income, and family composition (**Table 2**).

**Table 2 T2:** Comparability of intervention and control municipalities in the Nutrition Now project (data from 2017-2022).

Characteristics ^a^	Intervention (I)	Control (C)	Difference (I-C)
Population size (Q2, 2022) ^a^	45785	48024	-2239
Annual number of births (2021) ^a^	399	404	-5
**Population density (persons per km2) (2022) ^a^ **	**178**	**62**	**116**
Immigrants and Norwegian-born to immigrant parents, % (2022) ^a^	15	15	0
Asia, Africa, Latin America, Oceania except Australia and New Zealand, and Europe except the EU/EEA/UK	9	8	0
The EU/EEA, United Kingdom, USA, Canada, Australia and New Zealand	7	7	0
The top three countries of origin for immigrants and Norwegian-born to immigrant parents	4	5	-1
#1 - Poland	2.0	2.9	-0.8
#2 - Syria	1.0	1.1	-0.1
#3 - Lithuania	0.9	1.1	-0.2
Persons per family/household (2022) ^a^	2	2	0
Children of single parents, % (2018-2020) ^b^	19	18	2
Higher educational level, people over 16y (1y+), % (2021) ^a^	33	29	4
Higher educational level (long), people over 16y (4y+), % (2021) ^a^	8	7	2
Not in employment or education, people over 45y, excluding retirees % (2018-2020) ^b^	23	20	3
Median income per family after taxes in NOK (2020) ^a^	519000	522000	-3000
Sustained low-income households, % (2017-19) ^b^	12	11	1
Number of Healthcare centers (2022) ^c^	1	6	-5
**Number of ECEC (2022) ^c^ **	**54**	**39**	**15**
**Private ECEC, % (2022) ^c^ **	**81**	**54**	**28**
Children 1-2 years in ECEC, % (2020) ^a^	85	82	3
Children in municipal ECECs who receive special educational assistance, % (2020) ^a^	6	3	3

^a^Data from Statistics Norway (48, 49).

^b^Data from the Norwegian Institute of Public health (50).

^c^Data from the official homepages of the municipalities (51, 52). Bold numbers show characteristics where there are large discrepancies between the intervention and control municipalities.

### 2.5 Study participant groups and recruitment

The participant groups in this project are listed in **Figure 2**. All pregnant women and parents of 0-2-year-olds living in the intervention or control municipality are eligible for this study. For the sake of simplicity, we will refer to guardians/care givers/parents as parents although all are included in this notion. Further, all MCH nurses and midwives and ECEC leaders working in the intervention or control municipality, staff in ECECs in which the leaders have consented to participate, plus all other relevant municipality staff within public health in the intervention municipality are eligible to participate.

Pregnant women and parents of children aged 0-2 years will be recruited at 1) routine visits to the MCH centre by MCH nurses and midwives, 2) the municipality website and 3) the relevant ECEC’s website, with all routes leading to a registration website where participants are able to give digital consent. We have previously successfully recruited through MCH centres in a similar way (53). Persons from ethnic minority groups will be recruited for participation in in-depth-interviews, representing pregnant women, parents of 0–2-year-olds and parents of 1-2-year-olds in ECEC, *via* Non-Governmental Organizations and other arenas in the municipality using snowball sampling. ECEC leaders will consent on behalf of their ECEC and will then recruit team leaders at each unit and their staff by forwarding digital invitations to participate in the study. Midwives and public health nurses at the participating MCH centres and municipality stakeholders (public health workers, leaders) will be recruited by digital invitations from the research group.

The sample size in this study is capped by the annual birth rate in the two municipalities (~400 per group, e.g., a total of approx. 800 births each year). The primary effectiveness outcome, aspects child diet quality, exemplified by vegetable intake was used to check that the study would be sufficiently powered. In a previous efficacy trial of 298 1–2-year-olds, we observed a difference in the change from baseline to 6-month follow-up of +0.46 vegetable items per day in favour of the intervention group (n=148). Assuming a participation rate in this study between 50 and 80%, we anticipate a sample size of 510-820 from each municipality, of whom 100-160 will have potentially been exposed to all parts of the Nutrition Now resource (*in utero* to 2-years of age). The worst-case scenario, with a 50% participation rate and 100 participants being exposed to all parts of the Nutrition Now resource, would enable us to detect a difference in vegetable of intake between groups of 0.5 items per day (alpha of 0.05 and 80% power). We anticipate that several hundred participants will be exposed to the intervention to some extend enabling other comparisons between the intervention and control municipality, with larger participant numbers.

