## 3 Discussion

There are several potential challenges the project may face. Recruitment of participants and their continued participation is crucial for both the implementation and effectiveness part of this study. To reduce participant burden and maximise retention, we will keep the questionnaires short, easily comprehensible, and easy to complete. To avoid missing all data in the case of partly completed questionnaires, it will be possible to respond to only a few initial core questions, and still participate. Further, selection bias at recruitment between intervention and control sites may bias intervention estimates. In addition, although the original interventions have shown promising results in previous studies, the impact of the interventions might be more modest in a real-life setting. This dilution of intervention effect is a common finding in effectiveness studies and implementation trials (66), however the iterative approach to the implementation in our study is meant to reduce the chance of such dilution (54, 66).

A major strength of this study is the established efficacy in the original four interventions, the co-creation with the municipality, ECECs and MCH undertaken, and the established capacity and networks built by the research team. This experience will help address challenges along the way. The municipality setting and organization of ECEC and MCH are quite similar in all parts of Norway and thus, we expect that our findings related to the implementation will be generalizable to other Norwegian municipalities. Further, focusing on culturally diverse groups both in the effectiveness and implementation part, will render more culturally diverse and sensitive resources for future approaches.

*Nutrition Now* will break new ground by (i) systematically implementing and evaluating cumulative effects of successive dietary interventions in the first 1000 days of life in a real-life context, (ii) maximising interdisciplinary collaboration and integrating an anthropological approach with quantitative methods to truly adapt the intervention to context, (iii) bridging the previously described evidence-to-practice gap through rigorous scientific effectiveness evaluation of municipal implementation, (iv) harnessing the benefits of digital, video-based, technology to optimise access to dietary guidance in the municipalities, and (v) taking advantage of existing settings across sectors in municipal care to secure universal reach.

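### The worst-case power check counts 100 participants before any loss to follow-up, and its detectable difference of 0.5 items per day is no smaller than the 0.46 it is checked against

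*Protocol article*

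**What the plan says.** Section 2.5 explains that sample size is capped by the birth rate, and that the primary outcome, "exemplified by vegetable intake was used to check that the study would be sufficiently powered". It cites one reference effect, from an efficacy trial in children aged 1–2 years, where the text reads: "we observed a difference in the change from baseline to 6-month follow-up of +0.46 vegetable items per day in favour of the intervention group". Applying participation of 50% to 80%, it continues: "we anticipate a sample size of 510-820 from each municipality, of whom 100-160 will have potentially been exposed to all parts". For the low end, which it labels the worst case (half of those eligible taking part, 100 of them fully exposed), the section concludes that such a sample "would enable us to detect a difference in vegetable of intake between groups of 0.5 items per day (alpha of 0.05 and 80% power").

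Three other sections bear on this:

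- Section 2.9.1 (Effectiveness) makes the fully exposed group against the control municipality the main comparison. It adopts a treatment-policy estimand and plans sensitivity analyses for outcomes missing not at random.
- Section 2.3 (Study design) has a woman recruited in early pregnancy in April 2023 finishing in September 2025.
- Section 3 (Discussion) lists continued participation among the challenges and says that "the impact of the interventions might be more modest in a real-life setting". It adds that the iterative implementation is intended to make such dilution less likely.

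**The concern.** A worst case should be the least favourable situation that the study still has to cope with. Here only participation has been set to its low value. The same document expects follow-up of more than two years and incomplete outcome data, yet every one of the 100 is carried into the power figure. In addition, the check is meant to show sufficient power, but the difference it can detect is printed as 0.5 when the only effect offered for comparison is 0.46.

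At stake is how the main comparison will be read. If participation is near 50% and the result is null, a reader of section 2.5 could take it as coming from a study with 80% power for an effect of the size seen before, with losses already allowed for. The section does not establish that.

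**Working it through.** **Inputs from the protocol.** Alpha 0.05, power 80%, detectable difference 0.5, fully exposed n = 100 (low end) to 160 (high end), earlier effect 0.46, participation 50% to 80%.

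**Assumptions.** Two-sided test; two-sample comparison of means by normal approximation; equal proportional loss in both groups. The protocol gives no loss rate, so 10%, 20% and 30% are illustrative.

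**1. Reproducing the stated figure.** This cannot be done independently, because the SD and the comparator n are not given. Solving backwards, 0.5 has exactly 80% power if

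SD = 0.5 / [(1.960 + 0.842) × √(1/100 + 1/n_control)],

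which is 1.26 for 100 v 100 and 1.63 for 100 v 510. The stated 80% is therefore taken as given and used as the anchor.

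**2. What the 100 contains.** 100/0.50 = 200 and 160/0.80 = 200. Likewise 510/0.50 = 1020 and 820/0.80 = 1025. Participation is the only rate that separates the low and high figures, and the only one the section names.

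**3. Scaling from the anchor.** With equal proportional loss L, the SD and comparator n cancel:

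power = Φ(2.802 × (effect/0.5) × √(1 − L) − 1.960)

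detectable difference = 0.5/√(1 − L)

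| Assumed loss | Power at 0.5 | Power at 0.46 | Detectable difference |
|---|---|---|---|
| 0% | 80.0% | 73.2% | 0.50 |
| 10% | 75.7% | 68.6% | 0.53 |
| 20% | 70.7% | 63.5% | 0.56 |
| 30% | 65.0% | 57.8% | 0.60 |

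Example at 20% loss and 0.5: 2.802 × 0.894 = 2.506; Φ(2.506 − 1.960) = Φ(0.546) = 70.7%.

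For 80% power at 0.46, the number needed is 100 × (0.5/0.46)² = 118.1, so 119 analysed per group if the groups are equal, or 119/0.80 = 149 enrolled with 20% loss.

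**4. Rounding.** The 0.5 is printed to one decimal and could stand for 0.45 to 0.55. Power at 0.46 without loss is then:

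- if 0.45: Φ(2.802 × 0.46/0.45 − 1.960) = Φ(0.904) = 82%
- if 0.46: 80%
- if 0.50: 73%
- if 0.55: Φ(2.802 × 0.46/0.55 − 1.960) = Φ(0.383) = 65%

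Even at the favourable end (0.45), a 10% loss gives Φ(2.864 × 0.949 − 1.960) = Φ(0.757), about 78%.

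**5. High-participation case.** With 160 per group the detectable difference is 0.5/√1.6 = 0.395. Power at 0.46 is Φ(2.802 × 0.92 × √1.6 − 1.960) = Φ(1.300) = 90%, and 83% after 20% loss (128 per group).

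**6. Dilution, as an assumed sensitivity range only.** With n = 100, no loss and 0.5 exact, power is 49% if the effect were 25% below 0.46 (0.345) and 25% if it were 50% below (0.23). With 160 per group and 25% dilution it is 69%. The protocol gives no dilution rate.

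**The case against.** The strongest reply is that no arithmetic error has been shown. Section 2.5 claims 80% power at 0.5 with 100 fully exposed, and nothing here contradicts that; each lower figure answers a question the section did not put. That stands. A reader might infer that the stated 80% is false, and the protocol does not support this.

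Second, 0.46 rounds to 0.5, so the gap between the two may be a matter of printing. That stands in part: the 73% is not fixed by the document, and at the favourable end of rounding there is no shortfall at 0.46 before loss. It does not answer the attrition point.

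Third, 0.46 is a benchmark, not a declared target. It came from 6 months in 1–2-year-olds, whereas the main comparison concerns a longer, combined exposure that might do more. That is fair, but section 2.5 makes no such argument and offers no other effect. The Discussion's remark on dilution is itself hedged, and should not be read as a prediction of a smaller effect.

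Fourth, the base of 200 is back-calculated and its origin is not explained, so a loss allowance could in principle be hidden in it. That cannot be excluded, but the section attributes the 100 to participation alone and calls the exposure only potential.

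Fifth, the SD, comparator n and attrition allowance often sit in a full protocol or SAP that is not shown. Agreed: their absence is not the point. The point is the label and the conclusion that the article does print.

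**Conclusion.** The point holds at moderate severity. The 100 is a low-participation count before attrition, so calling it a worst case is not supported, and neither is the conclusion of sufficient power once losses occur or if 0.46 is the effect to be found. At an assumed 10% to 30% loss in both groups, power at 0.5 is about 76% to 65% and the detectable difference about 0.53 to 0.60. At 0.46 without loss, power is about 73% if 0.5 is exact, with a range of 65% to 82% from rounding. These results rest on a two-sided normal approximation and equal loss in the groups; they do not depend on the unstated SD or comparator n. A baseline-adjusted analysis might recover some power, but the protocol gives no correlation from which to judge.

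The shortfall belongs to the low-participation case; at 160 per group it is absent at 0.46, even after 20% loss. Two stronger readings should be resisted. A reader might infer that the study is more likely than not to miss its effect; that needs an assumed dilution of about 25% and 0.5 taken as exact, and the protocol fixes neither. A reader might also deduct children who do not attend ECEC, but the estimand is access to the resource, so non-attendance alone does not reduce the number analysed.

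**What to change.** In section 2.5:

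- Describe the 100 as the low-participation case before attrition, not as a worst case.
- State an expected attrition rate to child age 24 months, and give the detectable difference for the number then expected to have data. For example, it would be about 0.56 at 20% loss. Print it to two decimals so that it can be set beside 0.46.
- Report power at 0.46 for the same case (about 73% before loss if 0.5 is exact), and do not claim sufficient power for the earlier effect there. The 160-per-group figures can be shown alongside.
- If dilution is discussed, show it as an assumed sensitivity range.

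Printing the SD, sidedness and comparator n with the figure would let a reader reproduce it. The cost is a few sentences and a less favourable headline number. No participants are added, and the design, estimand and analysis are unchanged.
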